## Exclusion Criteria

An individual who meets any of the following criteria will be excluded from participation in this study:

1. HIV infection or any other immunosuppressive condition or medications.
2. Pregnant or lactating.
3. History of prior measles or immunologic evidence of prior measles in the absence of prior measles vaccination.
4. Severe anemia, defined as hemoglobin less than 8 g/dL.
5. Any acute or chronic condition which, in the opinion of the investigator, constitutes a contraindication to participation in this study.

**Co-enrollment guidelines:** Co-enrollment in other trials is restricted, other than enrollment on observational studies that do not exceed blood collection volume limits. Study staff should be notified of current and planned co-enrollment on any other protocol as it may require the approval of the principal investigator (PI).

## Inclusion of Vulnerable Participants

Children: We will only enroll children in this research protocol as this is the population most affected by measles and susceptible to the immune amnesia, which is the object of investigation in this study.

## Inclusion of Pregnant Women, Fetuses, or Neonates

Most of the females in our population will be below the age of menarche. Because pregnancy induces immunological changes that can confound the analysis of our data, pregnant persons will not be enrolled. Females who become pregnant during the study will be withdrawn from the study and no further study procedures will be done. Appropriate rabies vaccination PEP will be offered in the event of rabies exposure. Children less than of 1 year old will also not be included because they may retain maternal passive measles immunity for up to 1 year after birth.

## Screen Failures

Screen failures are defined as potential participants who consent to participate but do not meet inclusion/exclusion criteria for enrollment and are not subsequently enrolled in the study.

## Randomization

## Strategies for Recruitment and Retention

Participants will be recruited from the local population in each participating site’s catchment area. Site-specific processes for data mana will be provided in the SSA documents.

### Costs

There will be no costs associated with participation in this study.

### Compensation

Participants and the parent/guardian will be compensated for their time, transportation, and inconvenience based on locally acceptable and defined criteria at each site, as outlined in the SSA documents.

# PARTICIPANT DISCONTINUATION/WITHDRAWAL

## Participant Discontinuation/Withdrawal from the Study

Participants/parents/guardians are free to withdraw from participation in the study at any time.

An investigator may discontinue or withdraw a participant from the study for the following reasons:

- Significant non-compliance.
- If the participant meets an exclusion criterion (either newly developed or not previously recognized) that precludes further study participation, for example, pregnancy that occurs after enrollment.

The reason for participant discontinuation or withdrawal from the study will be recorded on the CRF.

## Lost to Follow-up

A participant will be considered lost to follow-up if he or she fails to return for follow-up visits according to criteria detailed in the MOP.

The following actions must be taken if a participant fails to return to the clinic for a required study visit:

- The site will attempt to contact the participant/parent/guardian to reschedule the missed visit, provide counsel on the importance of maintaining the assigned visit schedule, and ascertain if the participant or guardian/parent wishes to continue in the study. The participant may continue with the next scheduled visit, and the missed visit will not be considered a protocol deviation.
- These contact attempts should be documented in the participant’s study file.
- Should the participant continue to be unreachable until the time of the final study visit, he or she will be considered to be lost to follow-up.

# STUDY ASSESSMENTS AND PROCEDURES

The following study assessments and procedures will be performed according to the schedule provided in Table 1, Section 1.3.

## Screening Procedures

### Activities Performed Prior to Obtaining Informed Consent

Minimal risk activities that may be performed before the subject has signed a consent include the following:

- In-person, or telephone communications with prospective subjects or their parent/guardian.
- Review of existing medical records.
- Review existing radiographic images, if available.
- Review of existing photographs or videos, if available.
- Review of existing pathology specimens/reports from a specimen obtained for diagnostic purposes, if available.

### Activities Performed After a Consent for Screening Has Been Signed

The following screening procedures will be performed only after an informed consent has been signed by the participant/parent/guardian:

- Demographics review.
- Medical history collection.
- Physical exam, including vital signs (all participants) and mid upper arm circumference (MUAC; participants 12 to 59 months old).
- Concomitant medication.
- Vaccination history collection.
- Upper respiratory specimen (OP/NP swab) for measles PCR.
- Hemoglobin level.
- HIV testing.
- Urine pregnancy test for females of childbearing potential.
- Measles IgM/IgG serology.
- Optional photography.

All tests and procedures required to determine eligibility must be performed prior to enrollment; however, the Day 0 research blood sample and optional photography may be obtained once hemoglobin and pregnancy test (as applicable) results are confirmed, prior to confirmation of remaining screening test results. HIV testing will be performed with appropriate counseling per national policies. HIV testing for children younger than 24 months will be performed via PCR and repeated with Rapid Diagnostic Test (RDT) at Visit 11. HIV RDT will be performed at screening for participants 24 months and older and will not be repeated at Visit 11. Once all screening results are available, the participant will be notified of their eligibility status with a telephone call prior to the Day 14 study visit, if possible, or at the Day 14 study visit. If notified by phone, eligible participants will be scheduled for a Day 14 study visit and ineligible participants will be invited to site to discuss test results and referred for measles vaccination if both serum IgM and IgG antibody tests are negative.

## Description of Study Procedures

Measles vaccination: Participants who enroll as controls and are found to have a negative measles IgM and IgG serology will be provided measles vaccination by the study team or referred to receive the measles vaccine through the national immunization program to ensure these participants are protected against measles and do not develop a natural MeV infection during the study period. Control participants who have evidence of immunity to measles at screening will not be vaccinated.

Pregnancy test: Urine pregnancy testing will be performed.

Medical history, vaccination history, and concomitant medications: Medical history, vaccination history, and concomitant medications will be reviewed at screening and updated at indicated study visits (see Table 1).

Rabies vaccination: A 3-dose series of Sanofi Verorab (inactivated rabies vaccine) will be given according to the manufacturer’s standard dosing instructions. Participants will be randomized to receive the series at an early (Week 8) or late (Week 47) timepoint (see Table 1 for specific dosing timepoints).

Physical examination: Physical exam will include measurements of height, weight, vital signs (temperature, heart rate, and respiratory rate) for all participants and anthropomorphic measurement (MUAC) in children 12 to 59 months as indicated in Table 1, Schedule of Activities. At Visit 0, the physical exam will include an assessment for clinical signs and symptoms suggestive of acute MeV infection (e.g., skin rash).

Upper respiratory specimen: OP/NP swabs will be collected for PCR testing to diagnose measles and for research evaluations (see Section 7.3).

Blood draw: Blood samples will be drawn via finger/heel stick and/or venipuncture according to standard site procedures for laboratory evaluations and storage. The amount of blood drawn for research purposes at each visit (no more than 5 mL) will be within the limits allowed for research participants in each country and will be specified in the sites’ SSAs. If additional research samples or testing will be performed at certain sites, the tests, timing of sample collection, type of sample, and amount of blood, if applicable, must be described in the SSA and MOP.

Assessment of adverse events (AEs): AEs and serious adverse events (SAEs) that are related to the research procedures described in this protocol will be recorded, except for Grade 1 or 2 AEs that are expected. AEs and SAEs that in the investigators judgment are not at least potentially related to research procedures, for example those that are due to the natural course of the disease, will not be recorded as AEs/SAEs in the research database. All SAEs will be reported to local authorities and ECs per local reporting requirements.

Healthcare utilization: The study team will collect information on healthcare encounters, to the extent possible, during the year-long follow-up to determine if there is a difference in the number of encounters by study group.

Photography (optional): The study team may take photographs of the skin rash and/or Koplik spots during the screening/enrollment visit to document the signs of measles and non-measles. The photographs may include the face and eyes but will not include the whole face. All photographs will be stored securely.

## Biospecimen Evaluations and Correlative Studies for Research

Biospecimens and data collected under this protocol will be used to study immune amnesia following MeV infection and the immune response to a controlled immune stimulus (rabies vaccine). Of the 5 mL of blood obtained through venipuncture, plasma will be saved to measure rabies virus antibody responses and global antibody responses for immune amnesia. Cells will be saved to address the aims associated with B and T cells including ASCs. Stored specimens may be used to address research questions related to the main study objectives, for example, additional measurements of antibody responses by various assays, measurements of biomarkers that may influence vaccine responsiveness, additional analysis of ASCs, analysis of B and T cells, and other assays studying PBMC functionality. PBMCs will be collected in a subset of participants. The upper respiratory specimens (swabs) will be used for measles virus sequencing. Plasma or upper respiratory specimens (swabs) may be used for unbiased sequencing for viruses or bacteria. All sequencing and analyses will target pathogen (viral, bacterial, etc.) genetic material only, and no human genome data will be generated. All collected research specimens will be stored for later assessment. The specimen collection procedures will be specified in the Laboratory MOP.

## Management/Return of Results

Any clinically relevant test results such as a pregnancy, measles infection, measles IgG, measles IgM, measles PCR, HIV infection, or anemia will be shared with the participant. If the rabies neutralizing results are below the cutoff for protection, attempts to share the results with the participant may be made. Results from research laboratory assays (such as immunologic responses) will not be returned to participants/parents/guardians.

## Adverse Events

### Definitions

AE: Any untoward medical occurrence in a human subject, including any abnormal sign (for example, abnormal physical exam or laboratory finding), symptom, or disease, temporally associated with the subject’s participation in research, whether or not considered related to the subject’s participation in the research.

SAE: An SAE is any AE that:

- Results in death;
- Is life-threatening (places the subject at immediate risk of death from the event as it occurred);
- Results in inpatient hospitalization or prolongation of existing hospitalization;
- Results in a persistent or significant disability/incapacity;
- Results in a congenital anomaly/birth defect; OR
- Based upon appropriate medical judgment, may jeopardize the subject’s health, and may require medical or surgical intervention to prevent one of the other outcomes listed above in this definition (examples of such events include allergic bronchospasm requiring intensive treatment in the emergency room or at home, blood dyscrasias or convulsions that do not result in inpatient hospitalization, or the development of drug dependency or drug abuse).

Unanticipated Problem (UP): Any incident, experience, or outcome that meets all of the following criteria:

- Unexpected in terms of nature, severity, or frequency given (a) the research procedures that are described in the protocol-related documents, such as the IRB/EC-approved research protocol and informed consent document; and (b) the characteristics of the participant population being studied; and
- Related or possibly related to participation in the research (“possibly related” means there is a reasonable possibility that the incident, experience, or outcome may have been caused by the procedures involved in the research); and
- Suggests that the research places participants or others (which many include research staff, family members or other individuals not directly participating in the research) at a greater risk of harm (including physical, psychological, economic, or social harm) than was previously known or expected.

## Classification of an Adverse Event

### Severity of Event

AEs will be graded according to the “Division of AIDS Table for Grading the Severity of Adult and Pediatric Adverse Events” Corrected Version 2.1, July 2017 (<https://rsc.niaid.nih.gov/sites/default/files/daidsgradingcorrectedv21.pdf>).

### Relationship to Study Procedures

All AEs will have their relationship to study procedures assessed by an appropriately trained clinician based on temporal relationship and his/her clinical judgment. The degree of certainty about causality will be graded using the categories below.

**Related** – The AE is known to occur with the study procedures, there is a reasonable possibility that the study procedures caused the AE, or there is a temporal relationship between the study procedures and the event. Reasonable possibility means that there is evidence to suggest a causal relationship between the study procedures and the AE.

**Not Related** – There is not a reasonable possibility that the study procedures caused the event, there is no temporal relationship between the study procedures and event onset, or an alternate etiology has been established.

#### Expectedness

A clinician with appropriate expertise in infectious diseases and vaccination will be responsible for determining whether an adverse event (AE) is expected or unexpected. An AE will be considered unexpected if the nature, severity, or frequency of the event is not consistent with the risk information previously described for the study procedures. Expected AEs can be found in Section 2.3.1.

### Type and Duration of the Follow-up of Participants After AEs

AEs related to study procedures will be followed through resolution or until the local investigator judges that the event has stabilized, and no additional follow-up is required.

## Reporting

SAEs and UPs will be reported to Sanofi Pasteur according to the terms of the Clinical Trials Agreement.

Safety events will be tracked and submitted to the local IRB/EC according to each site’s/country’s requirements. These are described in the SSAs.

# STATISTICAL CONSIDERATIONS

This is a prospective, observational, longitudinal study. Children with acute measles and a control group without measles will be enrolled and followed for 1 year to examine the impact of MeV on the immune system. The impact will be measured using laboratory techniques that can assess the changes in total antibody diversity to multiple pathogens.

A controlled immune stimulus consisting of the rabies vaccine will be given to all participants with half receiving vaccines shortly after enrollment (at Week 8; “early” group) and the other half receiving them at a later timepoint (Week 47; “late” group). Antibodies to the rabies vaccine will be measured 5 weeks after the first rabies vaccine. This will provide information on the development of the immune response following MeV when the immune system is challenged with a controlled stimulus. The administration of early and late rabies vaccine will be randomly assigned and stratified by measles, by country group, and by age group.

## Statistical Hypothesis

1. There is a difference in antibody level changes from baseline to Week 13 between the acute MeV group and the control group.
2. There is a difference in rabies antibody titer between the acute MeV infection and the control groups at early and late timepoints.

## Sample Size Determination

The overall sample size will be 256 participants. We will accrue 128 acute measles participants (with half of these in age group 1-5 years and half in age group 6-15 years) and 128 control participants (with half in each age group).

Randomization to early and late rabies vaccine will be stratified by country, group, and age.

Power for comparison of rabies titers

The sample size calculation is based on detecting a difference in the rabies antibody geometric mean titer between the MeV and control groups. The rabies vaccine will be given to half of the participants at Week 8 and half at Week 47 post enrollment, and the rabies antibody titer will be measured 5-6 weeks after receipt of the first vaccine dose (Weeks 13 and 52, respectively). There will be a random assignment for receipt of rabies vaccination to the two timepoints with equal numbers in the acute measles young and old groups and control young and old groups. In this analysis only one measurement of rabies antibody titer per participant will be included and it will be the measurement 5 weeks after receiving the rabies vaccine.

The total study sample size will be divided into 8 cohorts stratified by measles status, age group, and rabies vaccine timepoint as outlined in Figure 1. The standardized difference that can be detected with 90% power using a 0.05 level two-sided test for different sample sizes by specific cohort are shown in [Table 2.](#_Table_2:_Standardized)

Table 2: Standardized detectable difference with 90% power using a 0.05 level two-sided test for different sample sizes.

| Sample size per specific cohort (total study sample size) | Comparison of MeV to control at either the early time point or late time point  (assume std=1) | Interaction between time and group.  Example: comparison of difference between early MeV and control vs late MeV and control  (assume std=(1^2^+1^2^)^.5^=1.4) |
| --- | --- | --- |
| 20 (160) | 1.05 | 1.47 |
| 30 (240) | 0.85 | 1.19 |
| 40 (320) | 0.73 | 1.02 |

The chosen sample size of 256 accounts for a 6.5% loss to follow up.

Power for multiplex serological methods for global antibody analysis (e.g. virscan):

We also present sample size calculations to show detectable change over time between groups in the panel of antibody measurements. This analysis will compare change in the panel of measurements from baseline to the 3-month blood draw between groups. The panel will contain numerous measurements, so we will use a Bonferroni correction to control the study-wide error rate at p=0.05. To be conservative, we will assume 1000 comparisons and plan to maintain the alpha level at a two-sided 0.05 rate (thus the power calculations will be performed with alpha=0.025/1000). We will perform the analysis separately for children aged 1-5 years and those aged 6-15 years. Table 3 gives the detectable between-group standardized difference (difference/std) with 90% power for different samples sizes with the Bonferroni correction for multiple comparisons. Here we combine the early and late rabies randomization groups since the rabies vaccination should not affect the comparison of other antibodies.

Table 3. Detectable standardized differences with 90% power.

The sample size is the number needed in an arm (measles or control), age group (young vs old (multiply by 4 for total sample size)

| Sample size per arm (total study sample size) | Standardized detectable difference |
| --- | --- |
| 40 (160) | 1.26 |
| 60 (240) | 1.00 |
| 80 (320) | 0.86 |

Note: The detectable difference of 1.00 that can be seen with a sample size of 240 is well within what the Mina paper found and is a reasonable sample size for this study.[[12](#_ENREF_12)]

Power for medical visit endpoint.

A particularly important secondary endpoint is healthcare encounters. We have calculated the power to compare health care encounters between the MeV and control groups for the selected sample size. One method to summarize healthcare encounters is to look at the proportion of participants in each group that had at least one medical visit. Using this measure, there would be 90% power to detect a difference in proportions of 0.5 versus 0.7 (control group versus MeV group, respectively) using a test of proportions. Note a proportion of 0.5 for the control group was used since this proportion gives the largest variance. Any larger or smaller proportions will allow smaller difference in proportions to be detected with 90% power. In the analysis, the Poisson test may be used which would be more powerful if participants have multiple healthcare encounters.

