# STUDY OBJECTIVES

The objectives for this study are:

| **OBJECTIVES** | **ENDPOINTS** | **JUSTIFICATION FOR ENDPOINTS** |
| --- | --- | --- |
| **Primary** | | |
| To determine if MeV infection induces a loss of pre-existing immunity (immune amnesia) to endemic pathogens at Week 13 after baseline in children in select African regions. | Mean change in a panel of antibody levels over 13 weeks as measured by multiplex serological methods (e.g. PhIP-Seq/VirScan or SeroChip) and targeted ELISAs for confirmation. | These methods detect antibodies against multiple diverse pathogens and epitopes and assess both neutralizing and non-neutralizing antibodies. |
| To determine the effect of MeV infection on immune response to a controlled immune stimulus (rabies vaccination) at early and late timepoints post-infection. | Proportion of subjects with rabies virus neutralizing antibodies (RVNA) titer ≥ 0.5 International Units per milliliter (IU/mL) as measured by rapid fluorescent focus inhibition test 14 days after the last PrEP regimen vaccination. | These tests will measure the immune response and functionality of antibodies raised against the rabies vaccine. |
|  | Proportion of subjects with an RVNA titer ≥ lower limit of quantification 5-6 weeks after the first rabies vaccine dose. |  |
|  | Geometric mean RVNA titer 5-6 weeks after the first rabies vaccine dose. |  |
| **Secondary** | | |
| To determine if there is an increase in healthcare system encounters in the year following enrollment in children with recent MeV infection compared to those without recent MeV infection. | Mean number of non-study sick visit healthcare system encounters during the 1-year follow-up. | Visits to the healthcare system for sick visits in the year following enrollment in children with recent MeV infection will help determine the clinical impact of the immune amnesia in an objective manner. |
| To determine if MeV infection induces a loss of pre-existing immunity (immune amnesia) to endemic pathogens at Week 52 after baseline in children in select African regions. | Mean change in a panel of antibody levels over 52 weeks as measured by multiplex serological methods (e.g., PhIP-Seq/VirScan or SeroChip) and targeted ELISAs for confirmation. | These methods detect antibodies against multiple diverse pathogens and epitopes. These represent the spectrum of both neutralizing and non-neutralizing antibodies. |
| **Exploratory** | | |

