### Analysis of Primary Endpoints

The analysis of the rabies antibody will be performed using a 0.05 level two-sided test as described in the sample size determination (section 8.2). 95% CIs around the parameter estimates will be provided. The panel of antibodies will be analyzed using t-tests and controlling the 2-sided 0.05 error rate via a Westfall Young approach as this will be more powerful than a Bonferroni correction.

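### The antibody panel is promised a study-wide error rate of 0.05 but is tested separately in two age groups, and nothing in the protocol makes them one error family

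*Protocol*

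**What the plan says.** Protocol section 8.2, in the part on power for the multiplex serology, states the goal: "we will use a Bonferroni correction to control the study-wide error rate at p=0.05". It sets the number of tests ("To be conservative, we will assume 1000 comparisons") and the level: "plan to maintain the alpha level at a two-sided 0.05 rate (thus the power calculations will be performed with alpha=0.025/1000". The next sentence splits the analysis: "We will perform the analysis separately for children aged 1-5 years and those aged 6-15 years". Table 3 gives the size per arm within one age group, with the total being four times that. At 40, 60 and 80 per arm it lists detectable differences of 1.26, 1.00 and 0.86 SD at 90% power.

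Section 8.5.2 replaces Bonferroni as the analysis method. The panel is analysed by t-tests, "controlling the 2-sided 0.05 error rate via a Westfall Young approach". Age is not mentioned there. Hypothesis 1 in section 8.1 compares measles cases with controls and has no age term.

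**The concern.** The promise covers the whole study, but the divisor appears to cover only one of two analyses. Section 8.2 derives the 1000 from the size of the panel, before it mentions age. If the whole panel is then tested once in the younger children and once in the older children, there are 2000 tests and two families at 0.05 each. The two families consist of different children, so their errors are close to independent and add up almost fully.

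The first primary objective is at stake. A report that measles lowers antibodies to some pathogen in at least one age group could carry nearly twice the false-positive rate that the protocol states.

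**Working it through.** **Inputs.** From section 8.2: two-sided 0.05 overall, 1000 comparisons, 90% power, and n = 40, 60 or 80 per arm within an age group. The method is a two-sample t-test with unit SD, solved from the noncentral t distribution with 2n - 2 degrees of freedom and noncentrality d × sqrt(n/2).

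**Step 1. Which level reproduces Table 3?**

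| Per-test level | n = 40 | n = 60 | n = 80 |
| --- | --- | --- | --- |
| Stated in Table 3 | 1.26 | 1.00 | 0.86 |
| t, two-sided 0.05/1000 (0.025/1000 per tail) | 1.260 | 1.010 | 0.866 |
| t, two-sided 0.05/2000 (alpha halved for two age groups) | 1.304 | 1.043 | 0.894 |
| t, one-sided 0.05/1000 | 1.216 | 0.976 | 0.838 |
| Normal approximation, two-sided 0.05/2000 | 1.229 | 1.003 | 0.869 |

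The first computed row is within 0.01 of the table throughout. The normal approximation at 0.05/2000 comes close at 60 and 80 but misses by 0.03 at 40. Taken over all three rows, the table was built with the full 0.05/1000 in each age group.

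**Step 2. Error rate over both age groups.**
- Two families, each held at exactly 0.05, in different children: 1 - 0.95^2 = 0.0975. The additive bound is 0.05 + 0.05 = 0.10.
- Bonferroni with 2000 independent tests at 0.00005: 1 - (1 - 0.00005)^2000 = 0.095. With correlated antibodies Bonferroni is conservative, so the rate would be lower.
- Westfall-Young run within each age group uses the correlation and spends close to its full 0.05, so the rate would be close to 0.0975.
- At 0.025 per age group: 1 - 0.975^2 = 0.0494.

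**Step 3. What the correction costs at 60 per arm (240 in total).**
- The detectable difference goes from 1.01 to 1.04 SD.
- Power at 1.00 SD goes from 0.891 to 0.855.

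**Step 4. For comparison, one age-stratified family.** With 120 per arm at a two-sided 0.05/1000, the detectable difference is 0.70 SD. Power at 0.70 SD is 0.90, against 0.36 within one age group. This assumes the same effect and SD in both age groups.

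**The case against.** The 1000 is a planning figure chosen to be conservative, and no actual panel size is given. If it was meant to count antibody-by-age tests, for example 500 antibodies in each of two groups, the 0.05 holds. Table 3 cannot exclude this, because it fixes the level per test and not what the 1000 counts. Section 8.5.2 also allows a joint Westfall-Young run, which would keep 0.05, and such detail is often left to the SAP. A claim confined to one age group is still controlled at 0.05 within that group.

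All of this stands as a limit on the claim. It does not remove the problem. The protocol itself fixes a study-wide promise, a divisor tied to panel size, and separate analyses, and no sentence reconciles them.

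A reader might go further and infer the same fault in the rabies analysis. The documents do not support that. Section 8.2 says "The total study sample size will be divided into 8 cohorts stratified by measles status, age group, and rabies vaccine timepoint", which describes how Table 2 was sized. Section 8.5.2 says "The analysis of the rabies antibody will be performed using a 0.05 level two-sided test". No sentence says that rabies titres are tested separately by age, and hypothesis 2 has no age term, so an error rate built on an age-split rabies test has no basis in the text. Section 3 does list threshold proportions as primary endpoints ("Proportion of subjects with an RVNA titer ≥ lower limit of quantification 5-6 weeks after the first rabies vaccine dose"), but section 8.5.1 plans proportions with confidence intervals or logistic regression and names no 0.05 test for them.

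A reader might also infer that the age split wastes power or leaves half the children unused. Both strata are analysed, enrolment is balanced by age on purpose, and each stratum has about 90% power for the protocol's own target of 1.00 SD. Whether to pool is a design choice.

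**Conclusion.** The point holds for the antibody panel: as written, section 8.2 does not deliver the study-wide 0.05 that it promises. On the natural reading, the chance of at least one false-positive antibody in either age group is up to 9.75%. It is close to that with Westfall-Young run within each age group, and lower with Bonferroni on correlated antibodies. This rests on two assumptions: that the 1000 is the count for one age group, and that the adjustment is run within age groups, as separate analyses imply. It would be too strong to say that the rate simply is 0.10, because the protocol fixes neither assumption. The finding does not extend to the rabies endpoints.

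**What to change.** In sections 8.2 and 8.5.2, state that the two age groups form one family for the primary panel analysis. Run Westfall-Young jointly over all antibody-by-age tests at a two-sided 0.05, or allot 0.025 to each age group. State whether the 1000 is per age group or covers both.

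If it is per age group, restate Table 3 at 0.05/2000: 1.30, 1.04 and 0.89 SD at 40, 60 and 80 per arm. Revise the note under the table to match, since power at 1.00 SD with 60 per arm becomes about 85.5% instead of 89%.

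The cost is a few sentences, three table entries and this slightly less favourable figure. No children, visits or samples are added.

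As an option rather than a correction, the sponsor could use a single age-stratified family of tests, which matches hypothesis 1 and detects about 0.70 SD with 120 per arm if effect and SD are common across ages. Age-specific results would then no longer be the primary test.
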